##### 2.9.2.2. Change in SMM and skeletal muscle index (SMI)

SMM was measured using dual-energy X-ray absorptiometry (DXA) at the baseline and 12th week visits. The subject removed all wearable items, except light clothing, and the examination proceeded by continuous transverse imaging from head to toe. SMI was calculated using the following formula: SMI = SMM (kg)/body weight (kg) × 100 at the baseline and 12th week visits. Changes in appendicular skeletal muscle mass (ASM) were measured using DXA at the baseline and 12th week visits, which is the sum of lean soft tissue from both the upper and lower extremities (Fig. 1). Change in ASM index (ASMI) was calculated using: ASMI = ASM (kg)/height2 (m2) at baseline and 12th week visits.

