##### 2.9.2.3. Amount of change in body fat

Body fat mass (BFM), percentage of body fat (%BF), and free fat mass (FFM) were measured using DXA. BFM and %BF were measured using DXA at baseline and 12th week visits. FFM was calculated using the following formula: FFM = LEAN (muscle) + bone mineral content at baseline and at the 12th week visit.

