##### 2.9.2.4. Amount of change in SPPB score

SPPB score was assessed at the baseline and sixth week visits. The change in score for each SPPB item (standing balance test, gait velocity test, and repeated chair stand test) were assessed at the baseline and at subsequent visits.

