##### 2.9.2.5. Amount of change in tumor necrosis factor-α (Tnf-α), interleukin-6 (IL-6), and insulin-like growth factor-1 (IGF-1)

TNF-α, IL-6, and IGF-1 levels were measured at baseline and 12th week visits.

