### 2.11. Statistical analysis

The main analysis group for efficacy evaluation used the per-protocol set (PPS), which consisted of protocol-compliant subjects who completed the clinical trial. The secondary analysis group used the full analysis set based on the intention to treat that all subjects who have been randomly assigned should be the targets of the evaluation. Safety evaluation was performed on the safety analysis set, which included subjects whose safety information was collected more than once.

The significance level of the statistical analysis was set at 5% and a 2-tailed test was used. Continuous variables represent the number of participants, mean, and standard deviation. Categorical variables were presented as frequencies and percentages. The subjects’ demographic information, medication, and medical history presented the results of the PPS analysis group. To address missing full analysis set values, the last observation carried forward analysis was applied. To deal with the missing values of PPS and safety analysis set, the observed case approach, which analyzes missing values without correction, was used.

The mean, standard deviation, median, minimum value, and maximum value for the amount of change in the SPPB score, score for each SPPB item, hand grip, SMM, SMI, ASM, ASMI, BFM, %BF, FFM, TNF-α, IL-6, and IGF-1 are presented for each group. The least square mean (LSmean) and standard error of the amount of change corrected for the independent variable of the fitted general linear model are presented for each group. Comparisons between groups was analyzed by fitting a general linear model. If any factor affecting the outcome variable is identified, the general linear model is fitted by adding the factor as an independent variable. For data bias, the Wilcoxon rank-sum test, which is a non-parametric method, was applied. In addition, an analysis based on stratification factors was performed. Changes in the experimental or placebo comparator groups will be analyzed using a paired t-test or Wilcoxon signed-rank test.

The number of subjects with adverse events, drug adverse events, serious adverse events, incidence rate, 95% 2-tailed confidence interval, and the number of occurrences will be presented for each group. Differences in incidence rates between groups are analyzed using the chi-square test or Fisher’s exact test.

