### 2.13. Stopping rules

Subjects may withdraw consent at any time for any reason without a disadvantage. In addition, a subject may withdraw for any reason. Subjects who discontinued the trial will complete the efficacy and safety assessments, with the exception of declining revisits.

Subjects may be withdrawn by the researcher if: a violation of the inclusion/exclusion criteria is found during the clinical trial; the clinical trial is discontinued due to a sudden accident; their safety might be compromised for any reason; a serious adverse event including excessive predicted symptoms or death occurs; they take contraindicated drugs or the researcher assesses whether the subject requires any treatment with contraindicated drugs; the researcher assessed that they were no longer able to participate in the study due to inappropriate dosing of IP; the subject is lost to follow up; they suffer a worsening of symptoms; and if researcher assesses they are no longer able to participate due to other reasons. The subject may withdraw from or discontinue the study if they or a legal representative withdraws consent, if they suffer an adverse event, or any other reason, such as their refusal to consume the IP or non-cooperation.

This clinical trial may be prematurely terminated at the subject’s request, the occurrence of an adverse event, serious protocol violation, or other plausible reasons. The principal investigator has the final authority to discontinue or modify a clinical trial. In this case, the principal investigator promptly notifies the monitor by phone or by writing.

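### LOCF in the full analysis set records zero change for dropouts without an exit measurement on outcomes scheduled only at baseline and week 12, weakening the only efficacy analysis of all randomised subjects

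*Protocol article*

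**What the plan says.** All references are to the protocol article.

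- **Rule for the full analysis set (Section 2.11):** "To address missing full analysis set values, the last observation carried forward analysis was applied".
- **Rule for the other sets (Section 2.11):** "To deal with the missing values of PPS and safety analysis set, the observed case approach, which analyzes missing values without correction, was used".
- **Role of the set (Section 2.11):** the per-protocol set is the main efficacy set. Of the other it says: "The secondary analysis group used the full analysis set based on the intention to treat".
- **DXA timing (Sections 2.9.2.2 and 2.9.2.3):** "SMM was measured using dual-energy X-ray absorptiometry (DXA) at the baseline and 12th week visits" and "BFM and %BF were measured using DXA at baseline and 12th week visits". Table 1 agrees.
- **Blood markers (Section 2.9.2.5):** "TNF-α, IL-6, and IGF-1 levels were measured at baseline and 12th week visits".
- **SPPB and grip:** both have a week-6 value. For SPPB, Section 2.9.2.4 says "SPPB score was assessed at the baseline and sixth week visits", and Table 1 shows baseline, week 6 and week 12. Grip is measured at every visit.
- **Exit assessments (Section 2.13):** "Subjects who discontinued the trial will complete the efficacy and safety assessments, with the exception of declining revisits". Table 1 also marks DXA and the blood markers as optional at an out-of-schedule visit.

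The analysed quantity in Section 2.11 is the change in each outcome, compared between groups with a general linear model.

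**The concern.** Where baseline is the only value before week 12, carrying the last observation forward means carrying baseline forward. The change then equals zero by construction, and the model treats that zero as a measurement. This is valid only if the outcome truly stays at its baseline level after dropout, and nothing in the article supports that for muscle mass, body fat or blood markers. For SPPB and grip the rule assumes instead that nothing happens between week 6 and week 12.

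Two things are at stake. A real week-12 difference is shrunk, so the confidence interval covers it less often than stated. And if the arms lose subjects at different rates while both change over time, filled-in zeros can create a difference where none exists.

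The full analysis set is the only efficacy analysis that includes everyone randomised, and so the only check on selection into the per-protocol set. If its values are partly artefacts, agreement or disagreement between the two sets is hard to interpret.

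**Working it through.** **Inputs from Section 2.10:** two-sided α 0.05 (sidedness from Section 2.11), power 85%, difference 1.0, SD 1.5 (there called a coefficient of variance), effect size 0.6667, dropout 20%, 52 per arm.

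**Assumptions not in the article:** the share of dropouts without an exit value (100% and 50% shown); the mean changes; any imbalance in dropout; dropout unrelated to outcome; and exit values that behave like week-12 values. The effect size of 0.667 SD is the SPPB planning value, used for DXA and markers only as an illustration because the article plans none for them.

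**1. The plan's own figure.** n = 2(1.960 + 1.036)² / 0.6667² = 40.4, so 41 per arm. 41 / 0.80 = 51.25, so 52 per arm and 104 in total. This reproduces.

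**2. Formulas for zero-filling.** Let d be the share of an arm set to zero, and let observed changes have mean μ and SD 1.
- Arm mean = (1 − d)μ
- Arm variance = (1 − d) + d(1 − d)μ²
- SE of the difference = √[(variance in arm 1 + variance in arm 2) / 52]

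**3. Equal dropout, mean changes 0 and 0.667 SD.**
- *All 20% lack an exit value (d = 0.20).* Estimate = 0.80 × 0.667 = 0.533. Variances are 0.80 and 0.80 + 0.16 × 0.444 = 0.871. SE = √(1.671/52) = 0.179. The bias of 0.133 is 0.74 SE. Simulated coverage of the true difference (20,000 runs): about 88%.
- *Half have an exit value (d = 0.10).* Estimate = 0.90 × 0.667 = 0.60. Simulated SE 0.188, coverage about 93.5%.

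**4. Equal dropout, no effect, no drift.** SE = √(2 × 0.80/52) = 0.175. Simulated type I error is 4.8%, so the test keeps its level.

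**5. Unequal dropout, no effect, common drift.** All dropouts are taken to lack an exit value.

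| Drift (SD) | Dropout | False difference (SD) | Simulated type I error |
|---|---|---|---|
| 0.5 | 25% vs 15% | 0.5 × (0.85 − 0.75) = 0.05 | about 6% |
| 0.5 | 30% vs 10% | 0.5 × (0.90 − 0.70) = 0.10 | about 9% |
| 1.0 | 30% vs 10% | 1.0 × (0.90 − 0.70) = 0.20 | about 19% |

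**6. SPPB and grip.** Suppose every dropout has a week-6 value and a fraction f of the week-12 difference is present at week 6. The expected estimate is 0.667 × (0.80 + 0.20f), which runs from 0.533 at f = 0 to 0.667 at f = 1. The article gives no basis for choosing f.

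**The case against.** Several stronger readings are tempting, and the article does not support them.

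- **Every dropout is set to zero.** A reader might infer this from the visit schedule alone. Section 2.13 has discontinued subjects assessed unless they decline to return, and Table 1 allows DXA and markers at an out-of-schedule visit. Only those who decline or are lost are set to zero, and the article does not say how many that will be.
- **Every DXA outcome is exactly zero.** SMI divides by body weight, which Table 1 repeats at week 6. If LOCF is applied to the components, SMI can change. The article does not say whether index or components are carried forward.
- **The standard error is simply understated.** The zero-filled SE (0.175) is below the SE from the 41.6 observed per arm, √(2/41.6) = 0.219. But 0.175 is the correct sampling SE of the zero-filled estimator, which targets a smaller quantity. With equal dropout and no effect, the error rate holds. The SE comparison also depends on drift: at 20% dropout it reverses once 0.80 + 0.16μ² exceeds 1.25, that is, at a mean change above about 1.7 SD.
- **The rule governs the headline result.** It does not. The main analysis is per-protocol with observed cases.

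It is also fair to say that nothing in a blinded, single-site trial with identical packaging predicts 30% vs 10% dropout, and that a drift from learning or placebo response is less natural for DXA and cytokines than for SPPB. Details such as imputation variables are usually left to the analysis plan.

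All of this narrows the point without removing it. LOCF is a rule the article states, not a gap left for the analysis plan, and it names no other missing-value method for the full analysis set.

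**Conclusion.** The concern holds in limited form, as a should-fix. For outcomes measured only at baseline and week 12, LOCF becomes baseline carried forward for any dropout without an exit measurement.

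The harms are attenuation, under-coverage of the true week-12 difference, and false differences if dropout is unequal and both arms drift. The first two depend on the share of dropouts without an exit value: 20% shrinkage if all of the planned dropouts lack one, 10% if half do. The third depends on dropout patterns and drift that are assumed here, so the 6% and 9% error rates illustrate what could happen and are not forecasts.

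The damage is confined to the secondary full-analysis-set results, including SPPB in that set. If the full analysis set were ever made the main set, the rule would reach the primary result. The current plan does not do this, so that possibility adds no weight here.

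**What to change.** Before unblinding, replace LOCF in the full analysis set.

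- **SPPB and hand grip:** a mixed model for repeated measures on weeks 6 and 12, adjusted for baseline and sex (the stratification factor), with the week-12 between-arm contrast as the estimate.
- **DXA outcomes and blood markers:** multiple imputation followed by ANCOVA, using exit measurements where they were taken.
- **LOCF:** keep it, if wanted, only as a labelled sensitivity analysis, and state whether SMI and ASMI are carried forward as indices or as components.

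The cost is revised wording, some programming and somewhat wider intervals. No new data are needed.

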### 2.5. Randomization and allocation concealment

Randomization and allocation will be performed by blind stratified block randomization based on the subjects’ sex at the baseline visit. Each subject was randomly assigned in a 1:1 ratio to either the test or placebo product. Randomization uses an interactive web response system. The randomization code enables reproduction through seed allocation. Each subject was assigned a unique IP number via the interactive web response system. Each subject was provided with a corresponding test or placebo product, according to their IP number.

The blinded sponsor, who was uninterested in this clinical trial, strictly managed and kept both the randomization codes and IP numbers closed until the statistical analysis.

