### 2.10. Sample size

To calculate the number of subjects, the change in SPPB score, which measures muscle functionality, was used. The type I error rate (α) was 0.05, and the type II error rate (β) was 0.15; thus, the power of the test (1-β) was 85%. The effect size of the difference in the amount of change in SPPB score between the experimental and placebo comparator groups was assumed to be 0.6667. Due to the lack of previous clinical trials, a meaningful change in SPPB score to calculate the number of subjects was assumed to be 1.0.^[22]^ The coefficient of variance for the difference in the amount of change in SPPB score was assumed to be 1.5. Based on this information, 41 subjects were included in each group. Considering a dropout rate of 20%, 52 subjects in each group. Therefore, 104 subjects were required.

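### The covariate and Wilcoxon rules leave the primary SPPB model open; one model should be named before the codes are opened

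*Protocol article*

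**What the plan says.** All the analysis statements are in section 2.11 (Statistical analysis) of the protocol article.

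- **Error level:** "The significance level of the statistical analysis was set at 5% and a 2-tailed test was used".
- **Model:** groups are compared by a general linear model, reported as LSmeans with standard errors. The model terms are not listed.
- **Covariates:** "If any factor affecting the outcome variable is identified, the general linear model is fitted by adding the factor as an independent variable".
- **Rank test:** "For data bias, the Wilcoxon rank-sum test, which is a non-parametric method, was applied". The triggering condition is not defined.
- **Stratification:** an analysis by stratification factor is announced as an addition. Section 2.5 gives sex as the only stratification factor.
- **Analysis sets:** the PPS is the main set for efficacy and the FAS is secondary.

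The same text covers the primary outcome (SPPB change from baseline to week 12, section 2.9.1) and the secondary outcomes. On blinding, section 2.5 says that the sponsor "kept both the randomization codes and IP numbers closed until the statistical analysis".

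**The concern.** The covariate rule makes the primary model depend on what is found to affect the outcome. It gives no candidate list, no selection criterion and no timing. It is not limited to variables measured before randomization, although Table 1 also schedules physical activity (IPAQ), diet recall and the lifestyle questionnaire at week 12. The Wilcoxon sentence adds a second route to a p-value, and nothing says whether that p-value replaces the model's or sits beside it.

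Several defensible p-values for the primary comparison can therefore exist, and the article does not say which one counts. Closing the codes until the analysis does not settle this, because nothing requires the model to be fixed before they are opened. If the result is positive, a sceptical reader cannot tell from the published plan whether the deciding model was fixed or selected, and the 5% level cannot be taken as assured.

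An article may leave a covariate list to the SAP. Here the article states a rule, and that rule is open-ended.

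**Working it through.** **1. Reproduce the planned sample size.** Inputs from section 2.10: "The type I error rate (α) was 0.05"; power 85%; a difference of 1.0 point; a value of 1.5 for variability, which acts as the SD because the difference is 1.0; and a standardised effect of 1.0/1.5 = 0.6667. The test is two-sided (section 2.11) and allocation is 1:1 (section 2.5).

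n per group = 2 × (1.960 + 1.036)² × 1.5² / 1.0² = 2 × 8.978 × 2.25 = 40.4, so 41.

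With 20% dropout: 41 / 0.80 = 51.25, so 52 per group and 104 in total.

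The stated 41, 52 and 104 are reproduced. Power at 41 per group is 85.5% by the normal approximation and 84.7% by the noncentral t. A one-sided test would need only 33, so the planned size does rest on a two-sided 5% test.

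**2. Simulate the type I error under different uses of the rules.** Null trials were simulated with 41 per group and 6,000 trials per scenario. The Monte Carlo standard error near 5% is √(0.05 × 0.95 / 6000) = 0.28 percentage points. Outcomes were normal with SD 1.5, rounded to whole points, or skewed. The number of candidate covariates was assumed to be 5, 10 or 20. Candidates were unrelated to the outcome, except in two extra scenarios with 10 candidates, where one had a correlation of 0.4 with it.

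| Use of the rules | Rejection rate at nominal 5% |
|---|---|
| One fixed unadjusted model, normal or rounded outcome | 4.7-5.6% |
| One fixed unadjusted model, skewed outcome | 3.6-4.5% |
| Mechanical and blind to group: add covariates with pooled p < 0.05, Wilcoxon if Shapiro-Wilk p < 0.05 | 4.6-5.8% |
| Smaller p of unadjusted model and Wilcoxon | 5.4-7.4% |
| Smallest p of unadjusted model, adjusted model and Wilcoxon | 5.7-8.3% |
| As above, plus any single-covariate model, 5 candidates | 6.6-7.9% |
| As above, plus any single-covariate model, 10 candidates | 8.0-9.9% |
| As above, plus any single-covariate model, 20 candidates | 9.0-10.8% |

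The Shapiro-Wilk trigger and the p < 0.05 entry criterion are assumptions made to run the check. The article names neither. The last three rows count any single candidate as eligible, because the article sets no criterion for when a factor has been found to affect the outcome.

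**3. Read the result.** Data-dependent selection that ignores treatment group does not by itself move the error away from 5%. The error rises only when the choice among models can follow the treatment p-value. Section 2.11 does not instruct that, but nothing in it or in section 2.5 excludes it.

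**The case against.** The strongest defence is that section 2.11 does not say when, by whom or from which data a factor is identified. Identification at a blinded data review fits the sentence as well as selection after unblinding, and an unseen SAP may fix candidates, criterion and timing. Followed mechanically, the rule costs nothing in type I error. That stands: inflation is possible, not built in. What remains is that the published rule permits both uses and names no deciding result.

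The size of any inflation also depends on assumptions. In a separate check with eight assumed candidates (5,000 null trials per scenario, 41 per group), picking was limited to covariates associated with the outcome. The error ran from 5.4% when no candidate was prognostic to 11.0% when four were. A single figure would mislead, so a range is given.

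Four stronger readings are tempting and are not supported:

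- **The model is chosen with allocation known.** Section 2.5 keeps the codes closed until the analysis. It leaves this possibility open but does not state it.
- **Wilcoxon would usually become the primary test, because SPPB change is a bounded whole number.** This needs a normality pre-test as the trigger, which section 2.11 never names. The sentence can also be read as describing a supplementary test. Against that reading, the next sentence marks the stratified analysis as additional and the Wilcoxon sentence carries no such mark.
- **Week-12 activity or diet would be used as covariates.** IPAQ and diet recall are also collected at baseline, and lifestyle at screening. The article does not say that week-12 values would enter a model. It only fails to rule them out.
- **The choice between PPS and FAS adds to the error.** Section 2.11 fixes the PPS as main and the FAS as secondary, so this choice is not open.

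**Conclusion.** The point holds as a weakness in a stated rule. The primary SPPB comparison has no single named model. Its covariates depend on an unspecified finding, the Wilcoxon condition is undefined, and neither sex nor baseline SPPB is named in the primary model.

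The two-sided 5% level is not guaranteed, but neither is it shown to be breached. It stays at 4.6-5.8% under mechanical use blind to group. It rises to roughly 6.6-10.8% if an analyst picks the most favourable permitted model, given 5 to 20 assumed candidates and 41 evaluable subjects per group. The planned 41, 52 and 104 are correct on their stated inputs and are not affected. The rule should be fixed. It is not a fatal flaw, because harm needs a use of the rule that the article does not prescribe.

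**What to change.** In section 2.11, replace the rule on adding identified factors with one primary analysis: a general linear model of SPPB change from baseline to week 12 on treatment, sex and baseline SPPB. State that:

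- the model is fixed before the randomization codes are opened;
- no variable measured after randomization enters it;
- its treatment p-value decides the trial;
- the Wilcoxon test and any model with other covariates are labelled sensitivity analyses that cannot replace that p-value.

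If non-normality is a worry, a robust standard error or a permutation test of the same model could be named in advance. Both are optional.

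The cost is a few sentences. No extra data or subjects are needed, and the sample size stays at 104. The change has its full value only if it is made before unblinding.

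### The primary model commits to neither sex (the stratification factor) nor baseline SPPB as a covariate and leaves adjustment to an undefined rule, which forgoes precision and leaves the choice of model open

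*Protocol article*

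**What the plan says.** Section 2.5 fixes the design: "Randomization and allocation will be performed by blind stratified block randomization based on the" sex of the subject, with 1:1 allocation. Section 2.9.1 and Table 1 place SPPB at baseline and week 12, and the primary outcome is the change between them.

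Section 2.11 then sets out the analysis in three steps.

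- The main comparison: "Comparisons between groups was analyzed by fitting a general linear model". No model term is named. The least-squares means are said to be corrected for the model's independent variable, but that variable is not identified.
- A covariate rule: a factor is added to the model if it is identified as affecting the outcome variable. The text does not say how, when or in which analysis set this is judged.
- The stratification factor, in a separate sentence: "In addition, an analysis based on stratification factors was performed".

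Section 2.10 sizes the trial on the change score: "To calculate the number of subjects, the change in SPPB score, which measures muscle functionality, was used". The standardized difference "between the experimental and placebo comparator groups was assumed to be 0.6667", and no covariate enters the calculation.

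**The concern.** Two variables are known before any outcome is seen and have a clear claim to a place in the primary model. Sex is one, because the randomization was restricted on it. Baseline SPPB is the other, because change usually depends on the starting value. Section 2.11 commits to neither.

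Three things are at stake.

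- **Precision.** A change score without its baseline as covariate has a larger error variance than the baseline-adjusted analysis whenever the correlation between baseline and follow-up is below 1 (variances equal).
- **Chance imbalance.** Subtracting the baseline does not fully remove a baseline difference between groups. Part of it stays in the estimate with the sign reversed.
- **Openness of the model.** The rule lets the primary model be settled after the outcome data are in hand. The same data could then give different primary estimates depending on which factors were judged to matter.

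**Working it through.** **Inputs from the documents.** Two-sided 5% level (2.10: "The type I error rate (α) was 0.05"; 2.11: "The significance level of the statistical analysis was set at 5% and a 2-tailed test was used"); power 85%, difference 1.0 point, coefficient of variation 1.5, 41 per group before 20% dropout (all 2.10). The coefficient of variation times the difference gives an SD of change of 1.5, and 1.0/1.5 = 0.6667.

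**Inputs assumed.** The documents give neither the baseline/week-12 correlation of SPPB (rho) nor the share of variance in change explained by sex (R²). Both are shown as ranges.

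**Step 1: the plan's own figure.** n per group = 2 × [1.5 × (1.960 + 1.036)/1.0]² = 40.40, rounded up to 41. Then 41/0.8 = 51.25, rounded up to 52, or 104 in total. The stated sample size reproduces as an unadjusted comparison of change scores. At 41 per group the power is 85.5% by the normal approximation and 84.7% by the noncentral t (noncentrality 1.0/(1.5 × √(2/41)) = 3.02, 80 degrees of freedom).

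**Step 2: baseline SPPB as covariate.** With equal variances σ² at both visits, the change score has variance 2σ²(1 − rho) and the baseline-adjusted outcome has σ²(1 − rho²). Their ratio is (1 + rho)/2. The residual SD is 1.5 × √((1 + rho)/2). Noncentral t, 41 per group:

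| Assumed rho | Variance ratio | Residual SD | Power | n per group for 85% |
|---|---|---|---|---|
| unadjusted | 1.00 | 1.50 | 84.7% | 42 |
| 0.3 | 0.65 | 1.21 | 95.9% | 28 |
| 0.5 | 0.75 | 1.30 | 93.1% | 32 |
| 0.6 | 0.80 | 1.34 | 91.5% | 34 |
| 0.7 | 0.85 | 1.38 | 89.9% | 36 |
| 0.8 | 0.90 | 1.42 | 88.2% | 38 |
| 0.9 | 0.95 | 1.46 | 86.4% | 40 |

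The last column is also by the noncentral t, which is why the unadjusted row shows 42 rather than the plan's 41. Using 80 rather than 78 degrees of freedom for the adjusted rows makes no material difference.

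**Step 3: what a baseline imbalance does.** If the groups differ by D at baseline, the expected change-score difference is the treatment effect minus (1 − rho) × D. At rho = 0.5, an SD of change of 1.5 implies σ = 1.5/√(2 × 0.5) = 1.5. One standard error of D is then 1.5 × √(2/41) = 0.33 points, and 0.5 × 0.33 = 0.17 points enters the estimate, against a target of 1.0.

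**Step 4: sex.** If sex explains a share R² of the variance in change and is balanced by the stratification, the adjusted residual SD is 1.5 × √(1 − R²). The unadjusted test then has a true two-sided level of 2 × [1 − Φ(1.96/√(1 − R²))]. Normal approximation, 41 per group:

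| Assumed R² | True level, sex omitted | Power, sex omitted | Power, sex included |
|---|---|---|---|
| 0.01 | 0.049 | 85.6% | 85.9% |
| 0.05 | 0.044 | 86.1% | 87.2% |
| 0.10 | 0.039 | 86.8% | 88.9% |

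Omitting sex is conservative, and including it gains about 0.2 to 2.1 points of power over this range.

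**The case against.** The strongest reply is that this is a condensed article. Covariate lists are usually left to the analysis plan, and least-squares means corrected for a model term suggest that adjusted models are intended. That stands as far as it goes: nothing in 2.11 forbids baseline SPPB or sex, and the sentence on stratification factors could mean a stratum-adjusted comparison as well as a by-sex display. But 2.11 is not silent. It states a conditional rule for covariates and places the one factor fixed by the design in an additional analysis. An analysis plan that fixed both covariates would have to override this text.

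A second reply is that validity is not at risk and the gain is uncertain. This also stands. The trial was sized without adjustment, omission of sex is conservative, nothing in the documents shows that sex predicts SPPB change, and at rho = 0.9 the gain from baseline is under 2 points.

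Four stronger readings are tempting, and the documents do not support them.

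- *The primary model ignores sex and baseline.* The text leaves this open.
- *Baseline imbalance passes in full into the treatment difference.* That describes an unadjusted comparison of week-12 scores. With change scores only the fraction (1 − rho) remains, in the opposite direction.
- *The type I error is inflated.* That would follow if the model were chosen for its result, and 2.11 does not say so. The text simply fails to prevent it.
- *The 12-point ceiling makes the loss much larger.* Entry is by grip strength with no SPPB limit (2.3.1), so high starters may enroll. The documents give no baseline mean or SD for SPPB, so no figure can be attached.

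**Conclusion.** The point holds as a failure to commit, and it should be corrected. Section 2.11 fixes a poor rule where a better one is available from data already collected. Under equal variances and an assumed rho of 0.3 to 0.9, a baseline covariate adds between about 11 and 2 points of power at 41 per group. The gain is present throughout that range, but its size cannot be settled from the documents. Sex contributes less. Its main justification is agreement with the randomization and a test at its nominal level. Fixing the model also closes the post hoc choice, a benefit that does not depend on rho. The trial's planned 85% power does not rest on this change.

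**What to change.** Before unblinding, amend 2.11 as follows.

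- Primary model: week-12 SPPB change = treatment + sex (stratum) + baseline SPPB.
- Each secondary efficacy endpoint: treatment + sex + that endpoint's own baseline.
- Report the least-squares mean difference between groups with its 95% confidence interval.
- Move any covariate identified later to a sensitivity analysis, and delete the conditional rule from the primary analysis.
- State what the analysis based on stratification factors is. If it is a by-sex display, label it as a subgroup analysis. A treatment-by-sex interaction is optional, and the trial is not sized for it.

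No new data or visits are needed, since sex, SPPB and the secondary measures are already collected. The cost is two degrees of freedom in the primary model and a wording amendment. Section 2.1 sends plan changes through IRB review. Section 2.5 keeps the randomization codes closed until the statistical analysis, so the change can still be made blind if it is made before then.
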